### Data management

All participants will be assigned an identification code to ensure the anonymization of their data. The investigator will maintain a subject identification list for the trial centre (subject identification codes with the corresponding subject names) to enable records to be identified. The sponsor, the trial site, and study staff will handle the subject’s personal and trial data according to the effective legislation regarding data protection. Any paper or electronic trial documents or data are confidential and will not be disclosed to third persons. In the informed consent form, the participants are informed that their medical records will be provided only to authorized monitors, auditors, or inspectors. Data will be collected in each participating centre using an electronic case report form (eCRF) within the REDCap system. The investigator is responsible for the data correctness, completeness, and filling in time. Only the principal investigators and the external Data and Safety Monitoring Board will have access to the trial dataset. External Data and Safety Monitoring Board will assess the trial progress, safety data, and the scientific validity of the results. Medical records of the subjects will be retained in the trial site for 25 years according to the European standards for clinical trials [28].

### Safety assessment

All patients who have been randomized and have taken at least one dose of treatment will be analysed for safety. Safety outcomes include bleeding, metabolic complications (ketoacidosis, hyperglycaemic hyperosmolar state, hyperglycaemia requiring new use of insulin), hypertension, new cardiac arrhythmia, allergic reaction, psychiatric disorders, new infections, and chorioretinopathy or blurred vision. All adverse events occurring after entry into the study and until hospital discharge will be recorded in the patient’s health record. An adverse event that meets the criteria for a serious adverse event between study enrolment and hospital discharge will be reported to the local Institutional Review Board. A serious adverse event for this study is any untoward medical occurrence that is believed by the investigators to be causally related to the study-drug and results in any of the following: life-threatening condition, severe or permanent disability, prolonged hospitalization, or a significant hazard as determined by the Data Safety Monitoring Board. Serious adverse events occurring after a participant is discontinued from the study will not be reported unless the investigators feel that the event may have been caused by the study drug.

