### Data collection and procedures study

All participating patients, regardless of the study arm into which they are randomized, will be monitored following general standard of care practices. Patients will be assessed once daily by local investigators.

Demographic data including age and sex assigned at birth, comorbidities, and the COVID-19 vaccination status from participants will be collected. Temperature, respiratory rate, cardiac frequency, peripheral capillary oxygen saturation (SpO2), respiratory support, partial pressure of arterial oxygen/fraction of inspired oxygen (PaO2/FiO2), quick Sequential Organs Failure Assessment (qSOFA) score, and the ordinal scale for clinical improvement of the World Health Organization will be monitored at least once daily. Biochemistry and haematological tests on days 1 and 7; and chest X-ray on days 1, 4, and 7; and discharge will be assessed (Table 2). Laboratory determinations will include haemoglobin, white blood cell, lymphocyte count, platelets count, glucose, blood urea nitrogen, serum creatinine, sodium, potassium, LDH, alkaline phosphatase, albumin, ALT, AST, total bilirubin, CRP, prothrombin time, D-dimer, ferritin level, interleukin-6, and procalcitonin. Patients will be followed up to 90 days after randomization.

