**Table 2 Tab2:**
[figure not shown]
Scheduled protocol activities

*Abbreviations: SpO2* Peripheral capillary oxygen saturation, *PaO2* Partial pressure of arterial oxygen, *FiO2* Fraction of inspired oxygen, *qSOFA* Quick Sequential Organs Failure Assessment, *WHO* World Health Organization

^a^Haemoglobin, white blood cell, lymphocyte count, platelet count, glucose, blood urea nitrogen, serum creatinine, sodium, potassium, LDH, alkaline phosphatase, albumin, ALT, AST, total bilirubin, CRP, prothrombin time, D-dimer, ferritin level, interleukin-6, and procalcitonin

Safety of the intervention will be actively evaluated by daily interrogation of the following common adverse effects of dexamethasone: hyperglycaemia, steroid-induced psychosis, gastrointestinal bleed, new infection, and chorioretinopathy or blurred vision [25].

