### Statistical analysis

Baseline demographic and clinical characteristics will be presented in both groups. Quantitative variables will be defined by mean and standard deviation. Continuous variables will be compared using Student’s *t*-test (normal distribution) or Mann–Whitney test (non-normal distribution). Qualitative variables will be defined by frequency and compared using the chi-squared test or Fisher’s exact test. The proportion of patients that meet the primary outcome will be calculated in the control group and the intervention group. The primary endpoint will be analysed using the chi-squared test comparing the unadjusted risk ratios in each arm. The estimates of risk ratios will be adjusted with multivariate analysis by logistic regression. Adjustment will be performed for age, gender, and history of diabetes, hypertension, or obesity which are the most important factors related to the mortality and disease progression in patients with COVID-19 [27]. Study site will also be included in the multivariate analysis. As a secondary analysis, survival analysis to show the effect of dexamethasone on the primary endpoint in each arm will be performed using Kaplan–Meier curves and log-rank test. A *p*-value of less than 0.05 will be considered statistically significant. Statistical analysis will be performed with the SPSS V28.0 software (SPSS, Inc. Chicago, IL, USA). CONSORT reporting guidelines will be followed to ensure that results are presented in a complete, detailed, and systematic way.

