Patients receiving glucocorticoids should be monitored for adverse effects. These include hyperglycaemia, an increased risk of infections (including bacterial, fungal, and *Strongyloides* infections) and prolonged viremia. However, in RECOVERY trial record, only four serious adverse events (0.19%) were deemed by the investigators to be related to dexamethasone (two of hyperglycaemia, one of gastrointestinal haemorrhage, and one of psychosis) [15]. Evidence is inconsistent on the viral clearance delay of glucocorticoid-treated COVID-19 patients [32, 33]. Nevertheless, it seems that a high or medium dose, but not a low dose of glucocorticoids, leads to viral clearance delay which seems clear [33]. The rates of infections in patients with COVID-19 receiving glucocorticoids are uncertain. In the same way as viral clearance, prolonged high-dose glucocorticoids increase the risk of the appearance of severe microbial infections [34]. At the proposed dose and period of treatment of dexamethasone in this study, low toxicity and good tolerability profiles are expected.

The major limitation of our study is that it is not blinded and lacks the use of a placebo. However, the primary endpoint of the trial is clear, causing the influence of placebo treatment to be smaller. In addition, with placebo treatment, the trial design would be more complex and the cost more expensive. Second, our study design will not allow us to conclude whether the administration of dexamethasone at different doses and for longer or shorter periods would have improved outcomes. Nevertheless, if our hypothesis is correct, our findings will provide novel insights about the management of patients with COVID-19 pneumonia without additional oxygen requirements and at risk of progressing to severe disease.

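### The listed hyperglycaemia safety outcome requires newly started insulin, so patients already on insulin cannot meet it, and it does not match the daily hyperglycaemia item elsewhere in the article

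*Protocol article*

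**What the plan says.** The Safety assessment section names the metabolic safety outcomes as "metabolic complications (ketoacidosis, hyperglycaemic hyperosmolar state, hyperglycaemia requiring new use of insulin". The third item, "hyperglycaemia requiring new use of insulin", depends on insulin being newly started. The first two carry no such condition.

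Four other places bear on this:

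- **Who can be enrolled.** The Exclusion criteria mention neither diabetes nor insulin. The Intervention section lets chronic medication continue at the physician's discretion. The Statistical analysis section expects patients with diabetes: "Adjustment will be performed for age, gender, and history of diabetes, hypertension, or obesity".
- **A second hyperglycaemia item.** The text under Table 2 describes "daily interrogation of the following common adverse effects of dexamethasone: hyperglycaemia, steroid-induced psychosis, gastrointestinal bleed, new infection". It sets no insulin condition.
- **General adverse events.** The Safety assessment section adds: "All adverse events occurring after entry into the study and until hospital discharge will be recorded in the patient’s health record". The Secondary outcomes section says that the incidence of adverse and serious adverse events will be reported.
- **Measured glucose.** Data collection schedules "Biochemistry and haematological tests on days 1 and 7", and glucose is in that panel for both arms. No listed safety outcome uses the values.

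**The concern.** A patient who takes insulin at home and needs much more of it during the trial has not started insulin, so the listed outcome does not register the change. For every other patient, the event is a decision to prescribe insulin, taken by staff who know the assigned arm. The Discussion accepts the lack of blinding because the primary endpoint is clear, and that argument does not carry over to a safety outcome defined by prescribing.

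The article treats this harm as important. The Discussion says "Patients receiving glucocorticoids should be monitored for adverse effects. These include hyperglycaemia", and two of the four drug-related serious events that it cites from the RECOVERY trial were hyperglycaemia. The same article reports that RECOVERY found no benefit in patients without respiratory support. In this population the harm side of the balance will therefore weigh heavily, and a reader will want to know what the hyperglycaemia count includes.

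**Working it through.** The plan states no figure for this outcome, so there is nothing to reproduce. The check compares the sections and then illustrates the possible size.

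**Step 1: the routes by which worsening glucose control can be counted**

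| Route | Open to a patient already on insulin? | Criterion stated in the article |
|---|---|---|
| "hyperglycaemia requiring new use of insulin" (Safety assessment) | No | Insulin newly started |
| Ketoacidosis, hyperosmolar state (Safety assessment) | Yes | Named emergencies |
| Daily hyperglycaemia question (under Table 2) | Yes | None given |
| General adverse event, until discharge (Safety assessment, Secondary outcomes) | Yes | None given |

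The first route is closed to insulin users by its wording. The third and fourth are open to them. The article does not say whether the first or the third supplies the reported hyperglycaemia count.

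**Step 2: share of events missed by the first route alone**

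The article gives no baseline insulin use and no hyperglycaemia rate, so all inputs here are assumptions. An event means worsening that calls for new or additional insulin. Let s be the share of an arm on insulin at baseline, r_u the event risk in non-users and r_i the risk in users.

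Missed share = s·r_i / [(1 − s)·r_u + s·r_i]

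With r_u = 10% and 126 patients per arm (Sample size section):

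| s (patients per arm) | r_i = 10% | r_i = 30% | r_i = 50% |
|---|---|---|---|
| 5% (about 6) | 5% | 14% | 21% |
| 10% (about 13) | 10% | 25% | 36% |
| 20% (about 25) | 20% | 43% | 56% |

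For example, with s = 10% and r_i = 30%: 0.03 / (0.09 + 0.03) = 25%.

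A second set of assumptions builds s from diabetes prevalence. If 15–25% have diabetes and 20–30% of those use insulin, s runs from 0.15 × 0.20 = 3% to 0.25 × 0.30 = 7.5%. With r_i = 60% and r_u = 10%:

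- At 3%: 126 × 0.03 × 0.60 = 2.3 missed and 0.10 × (126 − 3.8) = 12.2 counted, a missed share of 16%.
- At 7.5%: 126 × 0.075 × 0.60 = 5.7 missed and 0.10 × (126 − 9.5) = 11.7 counted, a missed share of 33%.
- If users carry the same 10% risk as everyone else, the missed share falls to 3–7.5%.

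The result therefore depends mainly on the assumed excess risk in insulin users, for which the article offers no figure.

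**Step 3: between arms**

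Randomization makes s equal in the two arms on average. Add D and C to the symbols for the dexamethasone and control arms.

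- Risk difference on the component, with all patients in the denominator: (1 − s)(r_uD − r_uC).
- Risk difference over all events: the same term plus s(r_iD − r_iC).
- The two differ by s(r_iD − r_iC), which the article gives no means of evaluating.
- The risk ratio on the component is r_uD/r_uC, the ratio among non-users. It differs from the overall ratio only if users have a different ratio.

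**The case against.** The strongest reply is that the article captures hyperglycaemia more widely than this one item. Hyperglycaemia is asked about daily with no insulin condition. All adverse events are recorded until discharge and their incidence is reported. The two metabolic emergencies apply to everyone. The list opens with "Safety outcomes include bleeding, metabolic complications", so it is not stated to be closed. New insulin is a coherent marker of clinically important new hyperglycaemia, and no hypothesis test, sample size or stopping rule described in the article depends on it. A condensed article may also leave an eCRF field or a glucose threshold to the full protocol.

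Much of this stands. A reader might infer that a worsening insulin user can never be counted, and the routes in Step 1 contradict that. A reader might also infer that the estimated harm is biased towards none. The documents do not show this: the definition applies to both arms, and unblinded decisions to start insulin could raise the count in the dexamethasone arm, which is the opposite direction. Nor does any figure in the article show that insulin users are the patients most exposed to this harm.

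Two things are not answered. The criterion is stated, not left out, so the missing full protocol does not excuse it; a fuller document with the same wording would have the same gap. And the broader routes give no rule for when raised glucose in an insulin-treated patient is an event, so they leave it to unblinded judgement.

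**Conclusion.** The point holds for one listed component and for its mismatch with the text under Table 2. As worded, the component cannot be met by enrolled patients already on insulin, short of ketoacidosis or a hyperosmolar state. The article has two different hyperglycaemia items and does not say which is tabulated.

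Overall undercounting of hyperglycaemia is a risk and is not demonstrated. The 5–56% range in Step 2 concerns this component alone, within one arm, and rests wholly on assumed rates. Those events may still be reported as general adverse events. The size and direction of any distortion between arms cannot be computed from the documents. The primary and secondary efficacy outcomes are unaffected.

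**What to change.** 1. Reconcile the Safety assessment section with the text under Table 2, and state which hyperglycaemia item is tabulated as the safety outcome.
2. For outcome classification only, define the component as hyperglycaemia requiring new insulin or an increase over the pre-admission insulin dose. This changes what is counted and leaves treatment as it is.
3. Record insulin use before admission, with its dose, at baseline.
4. Report the glucose already scheduled for days 1 and 7 by arm and by diabetes history, as an objective companion that does not depend on prescribing. Any threshold is for the sponsor to set in advance. The Intervention section foresees treatment after discharge, so say how patients without a day 7 value are handled.

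The cost is a revised sentence in the safety definitions and one eCRF field; no extra blood tests are needed. The reported hyperglycaemia rate will be somewhat higher, and routine in-hospital insulin changes unrelated to dexamethasone will add some noise. The widened component still rests on open-label prescribing, which is why the measured glucose should be reported beside it.

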### Intervention

Patients in the intervention group will receive an intravenous dose of 6 mg once daily from day 1 to day 3, followed by an oral dose of 6 mg once daily from day 4 to day 7 (Fig. 1). For participants unable to take an oral drug, intravenous dexamethasone will be given. We selected the same dose as the RECOVERY trial. Participants randomized to the control group will receive a standard of care. Given that pulmonary disease can progress rapidly in patients with COVID-19, patients will be closely monitored. For improving intervention adherence, a real-time medication monitoring system will offer monitoring of participants’ medication control combined with a short message service (SMS) after discharge. Study participants will receive the best standard of care according to the current COVID-19 Treatment Guidelines. Hospitalized patients who do not require supplemental oxygen can receive anticoagulants for the prevention of venous thromboembolic disease, gastric ulcer prophylaxis, hydration, antipyretics, antibiotics, and bronchodilators. Corticosteroids in patients requiring oxygen support in the control group will be received. In addition, remdesivir, tocilizumab, baricitinib, tofacitinib, and sarilumab will be considered in case of a worsening of disease status [13]. All chronic medication prescribed to the patient is permitted to continue at the discretion of the responsible physician/investigator.

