### Secondary outcomes

Secondary outcomes are:Requirement of non-invasive ventilation or invasive mechanical ventilationHospital length of stayAll-cause mortality during the 90-day period following enrolmentAll-cause readmission during the 90-day period following discharge

Local investigators will contact the patient or relatives by phone to ensure the status of the patient on day 90 after randomization. The lead investigator in each site will confirm the recorded 90-day readmission.

The incidence of adverse events and serious adverse events during the study period will be reported.

Results will be communicated at scientific meetings and submitted for publication in peer-reviewed international journals, regardless of the outcome.

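### Adverse-event recording stops at hospital discharge although dosing can continue at home and follow-up runs to day 90, so some harm goes unrecorded and AE observation time can differ between arms

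*Protocol article*

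**What the plan says.** The protocol article sets the safety window in the Safety assessment section: "All adverse events occurring after entry into the study and until hospital discharge will be recorded". For serious events it says: "An adverse event that meets the criteria for a serious adverse event between study enrolment and hospital discharge will be reported", the recipient being the local review board. One further sentence deals with late serious events: "Serious adverse events occurring after a participant is discontinued from the study will not be reported unless the investigators feel" that the study drug may have been the cause.

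Other sections look past discharge:

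- **Intervention:** intravenous dosing on days 1 to 3, "followed by an oral dose of 6 mg once daily from day 4 to day 7". Adherence is supported by a medication monitoring system "combined with a short message service (SMS) after discharge".
- **Data collection and procedures study:** "Patients will be followed up to 90 days after randomization". Below Table 2: "Safety of the intervention will be actively evaluated by daily interrogation of the following common adverse effects of dexamethasone". No counterpart after discharge is described.
- **Primary outcome:** a telephone contact at day 30 for patients already discharged, a review of the medical record before the call, and extraction of inpatient and emergency department revisits in the 30 days after discharge.
- **Secondary outcomes:** hospital length of stay, death to day 90 and readmission for 90 days after discharge, with a telephone contact at day 90. The same section adds: "The incidence of adverse events and serious adverse events during the study period will be reported". It does not define that period.

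**The concern.** Two separate problems follow from ending the window at discharge.

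**Incomplete capture.** A patient sent home before day 7 can still be taking study tablets. The plan then monitors whether the tablets are taken but describes no questioning about harm. The listed safety outcomes include new infections, psychiatric disorders, bleeding and metabolic complications, and some of these may appear at home without leading to a hospital contact.

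**A window that treatment can alter.** Discharge happens after randomisation, and length of stay is one of the trial's own outcomes. If the arms differ in stay, they differ in days at risk of a recorded AE. A comparison of AE proportions then mixes the effect on harm with the effect on stay, and the arm that leaves sooner looks safer.

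This matters here because the Background accepts that the earlier large trial of dexamethasone showed no benefit in patients not needing oxygen. The balance of benefit and harm in this population therefore depends on sound harm data, and mild or moderate events that nobody asked about are hard to recover later.

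**Working it through.** The article gives no figure to reproduce on this point. The check compares the stated windows and then illustrates the possible distortion.

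**Inputs from the article:** AE recording and SAE reporting from entry to discharge (Safety assessment); treatment on days 1 to 7 (Intervention); follow-up of 90 days (Data collection and procedures study).

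**Assumed inputs:** discharge days, mean stays and daily AE hazards. The article gives none of these.

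**Step 1. Dosing days after the AE window closes.** For discharge on day D, after that day's dose, the number is max(0, 7 − D).

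- D = 3: 7 − 3 = 4 of 7 doses (57%)
- D = 5: 7 − 5 = 2 of 7 doses (29%)
- D = 7 or later: none

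**Step 2. Share of the 90-day follow-up without AE recording.** The share is (90 − D)/90.

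- D = 3: 87/90 = 97%
- D = 7: 83/90 = 92%
- D = 14: 76/90 = 84%

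**Step 3. What is still captured after discharge.** Deaths to day 90, readmissions for 90 days after discharge, and inpatient or emergency revisits in the first 30 days after discharge. Harms leading to none of these are left out. Those that are caught arrive as outcomes or as extracted revisits, and the article does not describe recording them as AEs.

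**Step 4. Apparent risk ratio when the true hazards are equal.** With a constant daily hazard λ and a window of L days, the recorded AE risk is 1 − exp(−λL). The ratio compares the arm with the shorter stay with the other arm.

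| λ per day | Risk, 6 days | Risk, 8 days | Ratio 6 vs 8 | Ratio 5 vs 8 | Ratio 6 vs 6 |
|---|---|---|---|---|---|
| 0.01 | 0.058 | 0.077 | 0.76 | 0.63 | 1.00 |
| 0.02 | 0.113 | 0.148 | 0.77 | 0.64 | 1.00 |
| 0.05 | 0.259 | 0.330 | 0.79 | 0.67 | 1.00 |

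The true ratio is 1.00 in every row. A fixed window of equal length in both arms returns 1.00, as the last column shows for equal stays.

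**Step 5. Sensitivity to the constant hazard.** If events occur only in the first 7 days, the 8-day stay contributes 7 days at risk and the 6-day stay contributes 6. At λ = 0.01 the ratio is (1 − exp(−0.06))/(1 − exp(−0.07)) = 0.058/0.068 = 0.86. At λ = 0.05 it is (1 − exp(−0.30))/(1 − exp(−0.35)) = 0.259/0.295 = 0.88. The distortion is smaller but remains.

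**The case against.** The case on the other side has several parts.

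**A reader might infer that all post-discharge harm is missed.** The article does not support this. Deaths, readmissions and early emergency revisits are collected, so the gravest consequences are visible. The gap is confined to events that lead to none of these, plus the lack of AE classification for the rest.

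**A reader might infer that observation time does differ between arms.** Nothing in the article shows a difference in stay. The trial's hypothesis makes one plausible, but if stays are equal there is no distortion.

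**A reader might infer a contradiction between Secondary outcomes and Safety assessment.** The study period is not defined, so it can be read as the collection window. The two sections need a shared definition; a conflict is not proven.

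**A reader might infer that AEs stay outside the trial database because they go into the health record.** Recording an event there does not exclude transfer to the electronic case report form, which the Data management section names as the place for trial data.

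**The SAE rule may be less strict than it looks.** The discharge limit is attached to reports to the review board, and a later sentence allows some late reports. That sentence concerns participants who have left the study. Discharged patients are still in follow-up, so it does not clearly extend their window.

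**The sizes are constructed.** Discharge days, stays and hazards are all assumed, and from discharge on day 7 no dosing falls outside the window. This is right, and the figures are illustrations only.

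What stands is that the article states the discharge limit explicitly. It is therefore not a detail left to the full protocol.

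**Conclusion.** The concern holds in limited form. As stated, the rule leaves unrecorded those post-discharge harms that lead to neither death, readmission nor an emergency revisit, including any that arise while study tablets are taken at home. It also ties the AE window to length of stay.

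How many doses fall outside the window depends on the discharge day: 4 of 7 for discharge on day 3, none from day 7. The comparison between arms is distorted only if stays differ. With assumed mean stays of 6 versus 8 days and equal constant hazards of 0.01 to 0.05 per day, the apparent ratio is about 0.76 to 0.79. It would favour whichever arm leaves earlier, and the article does not show which arm that would be.

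The primary outcome, its ascertainment and its analysis are not affected. The point should be fixed, but it does not undermine the trial's main comparison.

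**What to change.** Record AEs and SAEs in both arms over one fixed window counted from randomisation that covers at least the whole treatment period. One workable choice is day 30 for all AEs and day 90 for SAEs; other fixed windows that cover treatment would also remove the dependence on discharge. Add structured AE questions to the day-30 and day-90 calls, and use the record review already scheduled to classify deaths, readmissions and revisits as AEs where they qualify. Define the study period in Secondary outcomes as this window, and align Safety assessment with it. No change to treatment is involved.

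The cost is a little more data entry and weaker recall of mild events by telephone. Recruitment began in June 2021 and was still open, so patients enrolled before the change will have less complete data. The report should say from which date the new window applied and show the AE comparison for patients enrolled before and after it.
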